**TREATMENT WITH NEUROMUSCULAR BANDAGE IN CHRONIC MECHANICAL LOW BACK PAIN. RANDOMIZED CLINICAL TRIAL.**

**ABSTRACT**

**Objectives.** To assess the efficacy of neuromuscular bandage (NMV) treatment on pain intensity, disability and quality of life in patients with chronic mechanical low back pain (CMLBP). The secondary objectives of the study are to evaluate the effect of treatment with VNM on the neuromuscular activity pattern of the extensor muscles of the trunk, abdominals and hamstrings and to analyze the influence of fear-avoidance beliefs, ideas of catastrophization, and presence of anxiety-depression in the efficacy of NMV in the treatment of these patients.

**Methods.** This is a randomized clinical trial in 62 patients with CMLBP, recruited from a specialized rehabilitation medical practice. Participation in the study will be offered consecutively to all those patients in whom the mobilization of skin / fascia in the clinical examination is shown as a "modifying factor of the effect of the treatment". They will be assigned randomly and with concealment of the randomization sequence to two intervention groups: the VNM group and the placebo bandage group. The duration of treatment will be 4 weeks, changing the bandage 4 times, weekly. In evaluating the results, on the one hand, alterations in the muscle activity patterns of the trunk extensors, obtained by surface electrode electromyography (SEMG), will be taken into account. On the other hand, data will be obtained by clinical interview and the use of validated questionnaires: Numerical Pain Scale (NPS), Roland-Morris Questionnaire (RM), SF-36, Fear Avoidance Beliefs Questionnaire (FABQ), Hospital Anxiety and Depression subscale (HAD) and Pain Catastrophization Scale (PCS). The assessment will be carried out in 3 evolutionary moments: pre-intervention, post-intervention and at 6 months. Both patients and evaluators will remain blind to the assigned treatment.

**BACKGROUND**

Nonspecific mechanical low back pain is currently one of the main health problems in developed societies, not only because of its high prevalence and the high percentage of chronicity (1,2,3), but above all because of the exponential growth of disability and disability secondary to the same that has occurred in recent decades, despite the prevalence having remained constant (4). Thus, in Spain between 1993 and 2004 there was an increase of 183% in total sick leave for this reason and it represents the main cause of disability in people under 45 years of age (1,5).

In Physical Medicine and Rehabilitation (MFyRHB) the treatment of patients with CMLBP is a real challenge. Despite this, the lack of quality clinical trials is a fact. At present, it can be stated that exercise therapy appears effective, although the evidence is based on low-quality studies, and that transcutaneous electrical neurostimulation is ineffective. However, insufficient data are available to draw firm conclusions about the clinical effect of other commonly used techniques such as back school education, low-power laser therapy, patient education, massage, traction, superficial heat / cold, lumbostats or manipulation ( 6.7).

In recent years we have witnessed the emergence in the world of physical therapy of a new technique developed by Kase, the Kinesio Taping method (8), known in Spain as neuromuscular bandage (VNM). Initially used in sports medicine, its scope of application has now been expanded so that it can be used in the daily treatment of numerous pathologies treated in MFyRHB (musculoskeletal conditions, neurological pathology, lymphedema and others). Although the exact mechanism of action is unknown for now, the clinical effects are the improvement of microcirculation and lymphatic drainage, muscle normotonification, joint support, activation of endogenous analgesic systems and influence on internal organs, with the great advantage of not limiting joint mobility (8).

Currently, despite its popularity, there is still little scientific evidence to support the use of VNM. During the last decade, the number of publications on its effect in areas as diverse as vascular pathology, neurological pathology, pediatrics and mainly in musculoskeletal pathology has progressively increased (9,10).

In relation to the efficacy of NMV in CMLBP, two RCTs have recently been published. Paoloni et al (11) evaluated the effect in terms of pain, disability and the phenomenon of lumbar flexion relaxation (FFRL) in the assessment with surface electromyography (EMGs) of NMV in CMLBP, comparing it with exercises and with a combination of exercises-NMV. NMV is just as effective as exercise therapy in reducing pain, but not in disability. On the other hand, in 28% of the patients, without differences between groups, the FFRL is recovered. Castro Sánchez et al (12) compared the effect in terms of pain, disability, resistance of the trunk musculature and kinesiophobia of NMV versus placebo. This RCT shows a statistically significant decrease in pain, although not clinically relevant (1 cm in the VAS) in favor of the NMV, as well as a significant improvement in the resistance of the trunk musculature compared to placebo. Although both RCTs do not show clinically relevant results, they do point to a positive trend towards the efficacy of NMV in CMLBP. Furthermore, limitations of the studies include the small sample of patients (39 patients), the absence of a placebo group, the short-term evaluation (1 month), and the single-blind design in the first and the short duration of the study. application of treatment (1 week) and evaluation of short-term results (1 month) in the second.

A central element in the current debate on best practice in the management of SCI is the efficacy of targeted versus generic treatments. Many clinicians and researchers believe that tailoring treatment to subgroups of patients positively impacts clinical outcome. A systematic review on the efficacy of treatments targeting subgroups of SCI patients provides cautious evidence supporting this therapeutic approach, based on the results of a high-quality study showing a statistically significant short-term clinical effect size with Mc Kenzie's kinesitherapy (exercises based on preferred direction). Symptoms and signs indicating a more likely response to a specific treatment are considered “modifiers of treatment effect” (13). According to Kase, the objective in applying the bandage is that it replicates the position of the therapist's hands on the patient's skin (8). In musculoskeletal pathology, during the clinical examination we can include manual mobilization of the patient's skin / fascia in different directions. If said mobilization modifies the symptoms or semiology of the patient, it can be considered as a “modifier of the effect of the treatment”. Despite this, none of the referenced studies (11,12) take this fact into account, using standardized treatment guidelines for all patients with CMLBP. It is possible that NMV is more effective when applied to subgroups of patients with CMLBP with detectable clinical features on examination.

Beyond studies on the effects of NMV treatment, the possible mechanisms on which these effects could be based are unknown. Kenzo Kase hypothesized that one of them could be the normalization of muscle activity. In the specific case of the lumbar region, electromyographic assessments of the neuromuscular activity of the extensor muscles of the back have in fact been frequently used as an objective measure of deficit, which helps in the diagnosis of patients with SCI. Most of the published works have focused on the study of the FFRL phenomenon. At the end of lumbar flexion, a myoelectric silence occurs in the spinal erectors, the load being supported by the passive structures (14). In patients with SCI, this silence disappears, probably because the contraction of the erectors would increase the stability of the spine, deficient due to the damage to its passive structures (15). The FFRL measured by SEMG seems to distinguish between subjects with SCI and controls with good precision (16). Likewise, it has been shown to be sensitive to relevant functional changes after treatment in patients with CMLBP (17). If the NMV really works through a normalization of muscle activity, at the level of the lumbar region it could cause alterations in the typical patterns of absence of relaxation shown by patients with pain, as the trial by Paoloni et al. Seems to point out. (11).

Taking into account all of the above, we have designed a study to assess the medium-term efficacy of CMLBP treatment with NMV, applied for 4 weeks to patients in whom mobilization of skin / fasciae is shown as a "modifying sign of the effect of treatment".

**HYPOTHESIS**

- Treatment with VNM in patients with CMLBP, in whose examination the mobilization of skin / fasciae is shown as a "modifying factor of the effect of the treatment", will produce a clinically relevant improvement in relation to pain, disability and quality of life in comparison with placebo bandage.

- The effect of treatment with VNM will be maintained in the medium term (6 months).

**OBJECTIVES**

- Main objective: To evaluate the short and medium term efficacy of NMV treatment in pain, disability and quality of life in patients with CMLBP, through a controlled and randomized study.

- Secondary objectives: 1) To evaluate the effect of NMV treatment on the muscle activity patterns of the trunk, abdominal and hamstring extensors obtained by electromyography with surface electrodes. 2) To analyze the influence of fear-avoidance beliefs, of catastrophizing ideas, of the presence of anxiety-depression, and of pain-coping strategies on the effectiveness of the VNM in the treatment of patients with CMLBP.

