**METHODS**

**Design**

Randomized, double-blind clinical trial, with 2 arms (VNM, Vplacebo), 3 assessing times (pre-treatment, at the end of treatment and follow-up at 6 months) and intention-to-treat analysis.

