**Power and sample size**

The study has been planned to obtain a difference of 3 points in the Roland Morris questionnaire since these values have been recognized as clinically relevant (18,19). According to the results of a previous sample of patients with CMLBP obtained in our center, the mean disability measured by the RM questionnaire had a SD of 3.2. Considering an alpha value of 0.05 and beta of 0.9 for comparison of two-tailed means, the required sample size is 24 patients per group to detect changes in disability. Considering losses of 20%, the study sample is established in 62 patients (20).

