**Data collection and analysis**

Sociodemographic data and clinical variables will be collected by clinical interview and by accessing the electronic history of the patient. The questionnaires as well as the EMGs will be obtained before the treatment, at the end of the treatment and at 6 months. Both the participants and the outcome assessors will be unaware of the allocation to each of the treatment arms. Primary outcomes will be obtained by intention-to-treat analysis.

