Descriptive statistics will be obtained by expressing continuous variables as mean (standard deviation) or median (quartiles) according to their normality or not, categorical variables in number (percentage) and expressing in all cases the 95% confidence interval. The normal distribution will be verified by the Kolmogorov test to determine the use of parametric or non-parametric tests. For comparison of continuous variables between groups, the Student's t tests or the Mann-Whitney U tests will be used and for categorical variables the Chi-square or Fisher's test according to the type of distribution. Intragroup changes in continuous variables at the end of treatment and at 6 months will be analyzed with Student's t test for paired samples. To assess whether there are differences between the two groups in pain, disability and in the different variables, analysis of covariance (ANCOVA) will be performed, one for each dependent variable. In all the tests, the independent variable will be the group while the covariate variable will be the baseline level of each dependent variable. It will be necessary to have comparable levels in both groups to correctly interpret the ANCOVA results. Therefore, several Student's t tests will be performed, one for each dependent variable, considering each group as an independent variable in each case. To assess whether the changes in the 2 groups occur differently, several ANOVAs will be performed, one analysis for each dependent variable. In all cases, the independent variable will be the group and the time in which the data are collected. In this analysis, only the possible presence of interactions is studied. In addition, the correlations between the study variables will be evaluated using Pearson's r or Spearmann's Rho according to normality. Two models of multiple linear regression will also be applied with pain and disability as dependent variables and in both models age, sex, pain, catastrophization, fear-avoidance, sick leave, evolution time and anxiety-depression as independent variables.

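### The main objective ranks three outcomes equally over two horizons with no named primary endpoint or decision rule, while the sample size covers Roland-Morris alone

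*Protocol*

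**What the plan says.** The Objectives section of the protocol has one main objective: "To evaluate the short and medium term efficacy of NMV treatment in pain, disability and quality of life in patients with CMLBP". The Hypothesis section names the same three outcomes. It expects that treatment "will produce a clinically relevant improvement in relation to pain, disability and quality of life in comparison with placebo bandage", and adds: "The effect of treatment with VNM will be maintained in the medium term (6 months". The Design section gives "3 assessing times (pre-treatment, at the end of treatment and follow-up at 6 months", so there are two post-baseline times.

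The section on power and sample size uses one outcome only: "The study has been planned to obtain a difference of 3 points in the Roland Morris questionnaire". It assumes that "the mean disability measured by the RM questionnaire had a SD of 3.2", arrives at 24 per group, and does not say at which visit the difference is to be shown. It gives no effect size or SD for the pain scale or the SF-36.

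Under Data collection and analysis, the protocol says "Primary outcomes will be obtained by intention-to-treat analysis", in the plural and without naming them. The between-group comparison is that "analysis of covariance (ANCOVA) will be performed, one for each dependent variable", adjusted for baseline. The Outcome measures section lists the instruments without ranking them. The Background section closes by describing the study as one of medium-term efficacy, whereas the main objective gives the short and medium term together.

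**The concern.** Three outcomes at two times make at least six comparisons, and more if the SF-36 is read scale by scale. The protocol does not say how these results combine into one answer: whether one success is enough, whether all are needed, or whether one comparison leads. Nor does the sample size match the objective, since it covers disability at one unspecified visit.

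Without a fixed rule, a mixed result, such as pain improved at four weeks but disability unchanged at 6 months, could be reported as support for the hypothesis or as failure of it. On this protocol alone, the choice could be made after the data are seen. Depending on the choice, the trial carries more false-positive risk than 5%, or less power than was planned.

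**Working it through.** **Inputs.** From the sample-size section: difference 3 points, SD 3.2, two-sided alpha 0.05, and a figure of 0.9 that the text labels beta but that reproduces the result when read as power. From Objectives, Hypothesis and Design: three outcomes and two post-baseline times. The correlations between test statistics are assumptions, because the protocol gives none.

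**1. The plan's own figure.** Normal approximation: n per group = 2 × (1.960 + 1.282)² × 3.2² / 3² = 23.9, so 24. This matches. The standardised effect is 3 / 3.2 = 0.9375. With 24 per group, power for one Roland-Morris comparison is 90.1% by the normal approximation and 88.9% by the t distribution. With 20% losses, 48 / 0.8 = 60 against the 62 stated; starting from 25 per group, 50 / 0.8 = 62.5. The sample size is sound for one comparison.

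**2. If any success counts.** For k independent tests at 0.05, the chance of at least one false positive is 1 − 0.95^k.

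- k = 3: 1 − 0.95³ = 14.3%
- k = 6: 1 − 0.95⁶ = 26.5%

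With equally correlated normal test statistics:

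| Assumed correlation | 3 comparisons | 6 comparisons |
|---|---|---|
| 0 | 14.3% | 26.5% |
| 0.5 | 12.5% | 21% |
| 0.7 | 11% | 16% |
| 0.8 | 10% | 14% |

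Under this rule power is not the problem: the chance of at least one success cannot be lower than the power for Roland-Morris alone.

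**3. If all six must succeed.** The error is then at or below 5%, because a false claim needs at least one false rejection and all the others as well. Power is the probability that all six are significant. Give every comparison the Roland-Morris power of 88.9% with 24 per group:

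- independent: 0.889⁶ = 49%
- correlation 0.5: about 65%
- correlation 0.7: about 72%
- correlation 0.8: about 76%

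Starting from the 90.1% of the normal approximation instead, the results are about 54%, 68%, 74% and 78%. All assume that pain and quality of life have the same standardised effect as Roland-Morris at both times. If one of them had an effect of 0.5 SD (assumption), power for that single test would be about 40%, and joint power could not exceed that.

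**4. If each comparison is its own claim, with the error controlled.** Bonferroni gives 0.05 / 6 = 0.0083 per test. Power per comparison falls from 90% to 73% at 24 per group (normal approximation). Restoring 90% needs 35 per group, and 70 / 0.8 = 87.5, so 88 patients instead of 62, again at a standardised effect of 0.9375 throughout.

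**The case against.** Testing order and multiplicity adjustment are commonly left to a statistical analysis plan, which is not available here, and the protocol nowhere says that each test is run at 0.05 without adjustment. That stands: the error rates above are conditional on an inference. It does not remove the point. Which outcome, at which time, answers the main objective belongs in the protocol, and this protocol states an objective that its own sample size does not cover.

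The count of six can also be disputed. The 6-month statement is a separate hypothesis that builds on the first, so three comparisons at one time is a fair reading. The plan also has a group-by-time ANOVA per variable that looks only at the interaction. This is why three and six are both shown; the error exceeds 5% in either case. One may add that planning on a Roland-Morris difference singles out disability in practice. It does, but the text never calls it primary and refers to several primary outcomes.

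Two stronger readings are tempting. A reader might infer that the 5% error and the planned power both fail. No single any-or-all rule does that: counting any success loses the error and keeps the power, and requiring all, which is the literal sense of the hypothesis, does the reverse. Both are lost only if every comparison is a separate unadjusted claim. A reader might also object that a Roland-Morris difference well below 3 points could reach significance. That is an ordinary property of a trial with about 90% power (1.96 / 3.24 = 0.60 of the target difference) and is no fault of this plan.

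**Conclusion.** The point holds in this form: the protocol names no primary outcome, time point or decision rule for an objective that spans three outcomes and two horizons, and it sizes the trial for one of these comparisons. Under any rule that gives all the stated comparisons equal standing, either the 5% error or the planned 90% power is lost. For correlations from 0 to 0.8, the loss is an error of 10–14% (three comparisons) or 14–26% (six) if any success counts. If all six are required, it is power of about 65–76% at correlations 0.5 to 0.8.

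These sizes rest on unadjusted 0.05 tests, a common correlation, 24 evaluable patients per group and, for joint power, the Roland-Morris standardised effect for every outcome. The documents confirm none of these for pain or SF-36, so the figures are illustrative. The mismatch between objective and sample size does not depend on them. The sample-size arithmetic itself is not at fault.

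**What to change.** Before unblinding, amend the protocol along these lines:

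- **Primary endpoint:** Roland-Morris at one time point, either end of treatment or 6 months, compared by baseline-adjusted ANCOVA at two-sided 0.05. The sponsor should choose and justify the time, reconciling the medium-term emphasis of the Background with the short and medium term of the main objective.
- **Key secondary outcomes:** Roland-Morris at the other time, the numerical pain scale, and one named SF-36 score, each with a stated time point, tested in a fixed sequence written down in advance.
- **All other outcomes:** exploratory.
- **Reporting:** give the Roland-Morris difference with its 95% confidence interval against the 3-point value, so that the hypothesis of clinical relevance is judged on the estimate and not on significance alone.
- **Objective, hypothesis and the reference to primary outcomes:** reword to match.

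The cost is protocol wording. The 24 per group, the total of 62, alpha and the planned power all stay as they are. The downside is that pain and quality of life become key secondary outcomes. If the sponsor wants them as separate co-equal claims, the Bonferroni figure of about 88 patients shows the order of the price.

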**METHODS**

**Design**

Randomized, double-blind clinical trial, with 2 arms (VNM, Vplacebo), 3 assessing times (pre-treatment, at the end of treatment and follow-up at 6 months) and intention-to-treat analysis.

**Participants**

Patients diagnosed with CMLBP recruited from the consultations of the Rehabilitation Service of a health area in Valencia that serve a population of 320,000 inhabitants will be invited to participate in the study.

They must meet the following inclusion criteria: 1) Age between 18 and 65 years. 2) LMC of 6 months minimum duration. 3) Amelioration of pain with mobilization of skin / fascia on examination. 4) Signature of informed consent.

The following will be considered as exclusion criteria: 1) Having had previous experience with NMV treatments. 2) Presence of neuropathic pain component (radiculopathy, lumbar canal stenosis). 3) Pain of specific origin (vertebral fracture, neoplasia in the spine or nervous structures, spondyloarthropathy, spondylodiscitis). 4) Previous spine surgery. 5) Mental retardation, severe mental illness, substance abuse or dependence, illiteracy.

**Power and sample size**

The study has been planned to obtain a difference of 3 points in the Roland Morris questionnaire since these values have been recognized as clinically relevant (18,19). According to the results of a previous sample of patients with CMLBP obtained in our center, the mean disability measured by the RM questionnaire had a SD of 3.2. Considering an alpha value of 0.05 and beta of 0.9 for comparison of two-tailed means, the required sample size is 24 patients per group to detect changes in disability. Considering losses of 20%, the study sample is established in 62 patients (20).

